### Consent

Informed consent will be obtained from all participants or a legal representative in case the former is impossible. As mentioned previously, this study involves two patient categories. In haematologic patients, lines are usually inserted electively for the administration of chemotherapy. Therefore, informed consent will be obtained before line placement. For the intensive care patient category, obtaining informed consent prior to CVC insertion is often not feasible. Therefore, for the intensive care setting patients may be included using the deferred consent procedure. We will randomise each patient at the ICU who meets the inclusion criteria directly before CVC placement. Informed consent from the legal representative will be requested as soon as possible. If informed consent is denied by a legal representative, the patient is excluded and data will no longer be used. Thenceforth, the patient is transfused according to the policy of the attending physician. If a patient dies before informed consent can be obtained, the data are used [36].

### Randomisation and blinding

Randomisation will be performed using a dedicated, password-protected, SSL-encrypted website with ALEA® software (TenALEA consortium, Amsterdam, The Netherlands). The researcher randomises the patient. Random block sizes are used. Block randomisation will be stratified per centre and per patient population (ICU vs. haematologic patients). Tunnelled lines are stratified per centre. Also, lines placed for dialysis/CVVH are stratified from central lines placed for other indications. This stratification takes place since dialysis/CVVH catheters are larger-bore catheters, made of stiffer materials and bear increased risk for bleeding [37].

The proceduralist, the physician who inserts the catheter, is blinded for treatment allocation. This blinding takes place to prevent bias in ordering platelet transfusion in case of a peri-procedural bleeding complication. The proceduralist is not directly involved in patient care of the included patient. Blinding is not feasible for the patient and the treating medical staff. Obtained photographs of the insertion site will be analysed for haematoma size and bleeding post hoc. This provides an additional blinded bleeding outcome.

### Treatment arms

Included patients will be randomised into one of two groups. One group of patients will be allocated to not receiving platelet transfusion prior to placement of the CVC, this is the experimental group. The other group of patients will be transfused with 1 unit of platelet concentrate prior to placement of the catheter, this is the comparison group. All platelet products will be manufactured, screened and stored according to local Dutch standards, (Sanquin Blood Bank). Platelet concentrates are prepared from pooled buffy coats from five donors, and re-suspended in plasma, after which pooled platelet concentrates are leukoreduced by filtration. All platelet products are stored, with gentle agitation at 20–24 °C, for up to 7 days in the Netherlands. All other care will be according to standard practice as indicated by the treating physician.

### Central venous catheter placement

All CVCs will be inserted percutaneously, under real-time US guidance, using the Seldinger technique. In the transfusion arm, catheters will be inserted as soon as possible after administration of 1 unit of platelet concentrate. The type of US device, catheters and (local) anaesthesia used is according to local hospital protocols. The puncture location will be determined by the puncturing physician. All procedures will be performed by experienced physicians, e.g. at least 50 previous line placements [38]. Proceduralists can be experienced residents or consultant physicians in intensive care, anaesthesiology, haematology, (interventional) radiology and surgery. Procedural details, such as arterial puncture, vein lesion and number of puncture attempts are recorded.

### Bleeding complications

Bleeding complications will be scored using WHO grades of bleeding specified for CVC placement, which are defined in Additional file 1. The WHO bleeding score is adapted according to Zeidler [28]. Grade 1 consists of mild symptoms not requiring any intervention; for example, local haematoma formation or wound oozing. Grade 2 bleeding is defined as mild symptoms requiring interventions, without haemodynamic instability or red blood cell (RBC) transfusion. For the current study, this includes procedure-related bleeding that requires more than 20 min of manual compression to stop. Grade 3 bleeding is defined as procedure-related bleeding requiring red cell transfusion. Grade 4 bleeding is defined as bleeding associated with hemodynamic instability or death, defined as CVC-related bleeding associated with severe hemodynamic instability (hypotension; > 50 mmHg fall or > 50% decrease in either systolic or diastolic blood pressure, with associated tachycardia (heart rate increase of > 20% for 20 min) and requiring RBC transfusion over routine transfusion needs or fatal bleeding [39].

Furthermore, a distinction will be made between minor and major bleeding. Minor bleeding is defined as WHO bleeding scale grade 1 or 2. Major bleeding is defined as WHO grade 3 or 4 bleeding. The proceduralist can administer rescue platelets at clinical indication. Rescue platelet concentrate can be given irrespective of treatment allocation, for which the proceduralist remains blinded.

In case of post-procedural bleeding, physicians are encouraged to undertake the following steps:

1. Inspection of the insertion site

2. Apply manual compression, for a maximum duration of 20 min

3. Consider a skin suture at the insertion site

4. Consider rescue platelet transfusion

5. Consider the possibility of a radiological of surgical intervention

### Protocol violation

If platelet concentrate is administered to patients assigned to not receiving platelet concentrate, patients will not be excluded. Reasons for additional transfusion are noted. Patients will be analysed according to intention-to-treat and per-protocol analyses. If line placement is unsuccessful due to technical reasons, data will also be analysed according to the intention-to-treat analysis. If blinding of the proceduralist is violated, this will be noted; however, patient data will not be excluded. If the 24-h time point is not completed, due to a CVC that is in situ for less than 24 h, or in the case that a patient deceases within this timeframe, obtained data will be analysed using missing data for the 24-h time point.

### Participant timeline and study flowchart

The participant timeline is presented in Fig. 2. The primary outcome of the study is procedure-related WHO bleeding grades 2–4, occurring within 24 h after the procedure.

**Fig. 2 Fig2:**
[figure not shown]
Informed consent will be obtained from all participants or a legal representative in case the former is impossible. Intensive Care patients may be included using the deferred consent procedure. We will randomise each patient at the intensive care unit (ICU) who meets the inclusion criteria directly before CVC placement. Informed consent from the legal representative will be requested as soon as possible. If a patient deceases before informed consent can be obtained, data is used

Secondary endpoints are subdivided into clinical outcome variables and health-economic-outcome variables. WHO grade-1 bleedings and subdivision on minor and major bleeding are scored as secondary outcome. Another clinical outcome variable is the validated HEME bleeding score [40]. Also, photographs of the insertion site at different time points are blindly scored. Other clinical variables include ICU and hospital length of stay (LOS), ICU and hospital mortality, transfusion requirements and occurrence of transfusion reactions such as TRALI and allergic reactions. Next to descriptive statistics, the effect of prophylactic platelet transfusion on the primary and secondary outcomes will be analysed using multiple logistic regression for patient-, procedural-, catheter- and transfusion-related characteristics. In patients receiving platelet transfusion, patient- and transfusion-related factors will be analysed to assess the relation to post-transfusion platelet increment. To investigate the relationship between bleeding events and platelet count (post-transfusion platelet count if applicable) we divide platelet count into five groups: 10–20, 20–30, 30–40, 40–50 and above 50. *P* values of 0.05 will be accepted as statistically significant, values will be reported with and without correction for multiple testing.

Health-economic outcomes are calculated in the cost-effectiveness analysis, where costs per procedure-related bleeding event (primary clinical outcome) will be estimated. The economic evaluation will estimate costs (saved) per PC transfusion avoided. Results will be extrapolated to the national level to estimate the total impact on the health care budget per annum for the Netherlands in terms of cost reduction and increase in procedure-related bleeding events.

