### Statistical considerations

We target to include 392 patients, with a potential limit of 462 patients to accommodate loss to follow-up and a possible dropout. The expected rate of severe peri-procedural bleeding incidents is around 0% [28, 33, 41–43]. Major bleeding is defined as WHO grade 3: gross blood loss requiring transfusion, or grade 4: debilitating blood loss (Additional file 1: Table S1). Considering the low complication occurrence, sample sizes that are by far unrealistic within the proposed study are required to demonstrate non-inferiority with an acceptable non-inferiority limit of (< 1%). We therefore also include WHO grade-2 bleedings in the definition of the primary outcome. As the observed bleeding events will concern predominantly grade-2 bleedings, and probably no or only incidental bleedings with more severe grades 3 or 4, an upper limit reflecting an absolute risk increase of 2.5% more bleeding events as the criterion to statistically demonstrate non-inferiority is considered both statistical and clinical acceptable. The sample size is increased by 2% to correct for loss to follow-up and by 15% to correct for dropouts, e.g. refusal of consent. Using a non-inferiority design, a sample size of 196 patients (per arm) and a percentage bleeding events of 1% in the control group and an expected percentage bleeding events of 1% in the experimental group will result in a power of 80% to exclude that there is a significant bleeding rate in the experimental arm (> 3.5% bleedings, absolute risk increase 2.5%, two group *t* test with a 0.05 two-sided significance level). As we do not anticipate any loss to follow-up – considering the short time-span of the study – we therefore intend to enrol 392 patients in total.

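### Cost per bleeding event, one of three planned economic outputs, is a poor summary when about 2 bleeds per arm and no difference between arms are expected

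*Protocol article*

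**What the plan says.** The health-economic plan is the last paragraph of the section Participant timeline and study flowchart (the text after Fig. 2). It names three outputs:

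1. A cost-effectiveness analysis "where costs per procedure-related bleeding event (primary clinical outcome) will be estimated".
2. A second ratio: "The economic evaluation will estimate costs (saved) per PC transfusion avoided".
3. A national budget impact, expressed "in terms of cost reduction and increase in procedure-related bleeding events".

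The first output is not described as incremental, as a difference, or as a cost per event avoided. Costs are listed among the secondary endpoints.

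Statistical considerations fixes what the trial expects for the outcome in that ratio: "a percentage bleeding events of 1% in the control group and an expected percentage bleeding events of 1% in the experimental group", with 196 patients per arm, 80% power and a margin of 2.5 percentage points.

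**The concern.** The first output uses as its effect measure the one outcome on which the arms are designed not to differ. In a comparative cost-effectiveness analysis, cost per unit of effect normally means the difference in mean cost divided by the difference in effect. If the expected difference is zero and events are few, the quotient may not exist. Where it exists, one or two patients can set its sign and size.

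The sign matters because the two signs mean opposite things. If omission saves money, a positive ratio is a saving bought with extra bleeds, and a negative one is a saving with fewer bleeds. Values from the two situations cannot be ranked on one scale, and an ordinary interval for the ratio that spans both cannot be interpreted.

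The result the trial hopes for, non-inferior bleeding with lower cost, is where this measure behaves worst.

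**Working it through.** **Inputs.** From Statistical considerations: 196 per arm, 1% in each arm, margin 2.5 percentage points, 80% power, and an upper limit of 462 patients (231 per arm). The documents give no per-patient cost, so the mean saving per patient from omission stays as a symbol S, assumed positive.

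**The plan's own figure.** n per arm = (z for alpha + z for power)² × 2 × 0.01 × 0.99 / 0.025² = (1.645 + 0.842)² × 0.0198 / 0.000625 = 195.9, so 196. This confirms that the 1% v 1% assumption underlies the stated size. It uses one-sided alpha 0.05. The text labels the level two-sided, which is a separate matter and not needed here.

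**Reading A: incremental ratio.** Let D be bleeds in the no-transfusion arm minus bleeds in the transfusion arm. The ratio is S / (D/196).

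- Expected events: 196 × 0.01 = 1.96 per arm. The expected value of D is 0.
- D = +1 or −1 gives +196 S or −196 S. D = +2 or −2 gives +98 S or −98 S. D = 0 gives no value.

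Exact enumeration of two independent binomial counts gives:

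| Per arm | No transfusion v transfusion | D = 0 (undefined) | D > 0 | D < 0 |
|---|---|---|---|---|
| 196 | 1% v 1% | 21.0% | 39.5% | 39.5% |
| 231 | 1% v 1% | 19.2% | 40.4% | 40.4% |
| 196 | 0.5% v 0.5% | 31.2% | 34.4% | 34.4% |
| 196 | 2% v 2% | 14.6% | 42.7% | 42.7% |
| 196 | 2% v 1% | 12.4% | 72.8% | 14.8% |
| 196 | 3.5% v 1% | 3.3% | 94.0% | 2.7% |

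The first row is the plan's own assumption. The second is its upper recruitment limit. The next three are illustrative, and the last puts the true difference at the margin. In the first row the counts differ by at most one event in 57.1% of trials.

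**Reading B: each arm's cost divided by its observed bleeds.**

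- Chance of no bleed in one arm: 0.99^196 = 0.1395, about 14%.
- Chance that at least one arm has none: 1 − (1 − 0.1395)² = 1 − 0.7405 = 0.26.
- Chance that neither arm has any: 0.1395² = 0.0195, about 2%.
- Direction: take an arm with total cost C and k bleeds. One more bleed costing c changes the ratio from C/k to (C + c)/(k + 1), which is lower whenever c < C/k. With 196 patients and k = 2, C/k is 98 times the mean cost per patient. The ratio therefore falls with an extra bleed unless that bleed costs more than 98 average patients, and a lower value does not mean better value for money.

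**A measure that avoids this.** Incremental net monetary benefit is S − V × D/196, where V is the value placed on avoiding one bleed. At D = 0 it equals S. Each extra bleed shifts it by V/196. It always exists and moves in one direction.

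**The case against.** The strongest objection is that the text never calls the ratio incremental. The next sentence does mark its own ratio as comparative, with a saving and an avoided transfusion, so the authors used such words where they wanted them. A reader might infer that the plan defines a ratio with a zero denominator. The documents do not support that, and the 21% figure depends on Reading A. This stands, and it is why both readings were worked through. Reading B has its own faults, so the ambiguity does not rescue the measure. A narrower meaning, the mean cost of treating a bleed pooled over both arms, would be undefined in only about 2% of trials. But it would rest on about 4 bleeds (2 × 1.96 = 3.92), and it would be a unit cost that compares nothing between arms.

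A reader might also infer that a successful trial could end with no usable economic result. The documents do not support that either. The saving per transfusion avoided has a stable denominator, because the arms differ by design by one unit per patient. The budget impact gives costs and bleeds as separate quantities.

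A journal article also leaves economic methods to fuller documents. This is a fair answer to any complaint about missing bootstrap or acceptability-curve detail, and none is made here. The point concerns a measure that the article does state. It is also true that an arm that is cheaper with fewer bleeds would ordinarily be reported as dominant. That eases the problem of negative ratios, but not equal counts or the instability of positive ones.

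**Conclusion.** The point holds for one of three secondary economic outputs. Under the plan's own assumption, the incremental ratio is undefined in about one trial in five and has a sign decided by chance in the rest. The per-arm ratio is undefined for at least one arm in about one trial in four and generally moves in the wrong direction. The incremental problem persists at 231 per arm and at equal rates from 0.5% to 2%. It fades only as the true difference nears the margin.

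The figures assume independent binomial counts, one per arm, and a positive saving S. Patients may be randomised more than once, which the calculation ignores.

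The sample size, the primary non-inferiority test, the saving per transfusion avoided and the budget impact are untouched. Severity is minor to moderate.

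**What to change.** Replace the cost per bleeding event by:

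1. the difference in mean cost per patient and the difference in bleeding risk, each with its interval and with their joint uncertainty shown, for example on the cost-effectiveness plane;
2. the incremental net monetary benefit of omission over a stated range of values per bleeding event avoided.

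Keep the saving per platelet transfusion avoided as the main economic ratio, and keep the budget impact as planned.

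For the bleeding difference, choose a method that copes with an arm without events, such as a score interval, with a model-based simulation for the joint uncertainty. A plain bootstrap of an arm with no bleeds never produces one and so understates the uncertainty. If a cost per bleed is still wanted as an input to the budget impact, define it as the mean cost of treating a bleed and state the number of bleeds behind it.

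The cost is a change of wording and a little more analysis, with no new data. The drawback is that the documents give no value per bleed avoided, so the range must be assumed. It should be fixed before the costs and bleeds are compared by arm, so that the summary is not chosen after the result is known.

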### Data collection

Inclusion is based on platelet count determined in the 24 h prior to randomisation. Baseline parameters, such as age, gender, height, weight and Body Mass Index (BMI), are collected. Recorded clinical parameters include date of admission, diagnosis, cause of thrombocytopenia, indication for CVC, use of defined confounding medication, hepatic- and kidney failure, diffuse intravascular coagulopathy and fever. For intensive care patients, also APACHE score, admission diagnosis and information about setting during admission are obtained. For haematologic patients, information about the haematologic condition and the phase of therapy is collected. In all patients, the most recent PT (INR), aPTT and haemoglobin levels, prior to randomisation are recorded. Information about the CVC, such as type, indication and diameter, is collected. Procedural details, such as insertion site, number of punctures, inadvertent arterial puncture, manual compression and the administration of ‘rescue platelets’, are recorded. According to standard care, blood is collected at 1 h and 24 h after CVC placement. In this way the effect of the platelet concentrate, if applicable, can be measured. A photographic image of the insertion site is taken prior to CVC placement, as well as directly post procedural and at 1 and 24 h after CVC placement. Clinical bleeding will be assessed at these same time points. All administered transfusion of blood products will be registered, as well as their clinical indication. All radiologic and surgical interventions will be documented.

### Follow-up

The follow-up time for the primary outcome is 24 h. Patient information about both ICU and hospital discharge or death, whichever comes first, are collected.

### Data management

An eCRF for the PACER trial in Open Clinica is developed. All participating centres have 24-h access to the eCRF. Data can be entered continuously for all participating patients. The principle investigator has access to the filled-out eCRFs. If data are entered incompletely or incorrectly, the principle investigator can contact the participating centres for clarification.

### Statistical considerations

We target to include 392 patients, with a potential limit of 462 patients to accommodate loss to follow-up and a possible dropout. The expected rate of severe peri-procedural bleeding incidents is around 0% [28, 33, 41–43]. Major bleeding is defined as WHO grade 3: gross blood loss requiring transfusion, or grade 4: debilitating blood loss (Additional file 1: Table S1). Considering the low complication occurrence, sample sizes that are by far unrealistic within the proposed study are required to demonstrate non-inferiority with an acceptable non-inferiority limit of (< 1%). We therefore also include WHO grade-2 bleedings in the definition of the primary outcome. As the observed bleeding events will concern predominantly grade-2 bleedings, and probably no or only incidental bleedings with more severe grades 3 or 4, an upper limit reflecting an absolute risk increase of 2.5% more bleeding events as the criterion to statistically demonstrate non-inferiority is considered both statistical and clinical acceptable. The sample size is increased by 2% to correct for loss to follow-up and by 15% to correct for dropouts, e.g. refusal of consent. Using a non-inferiority design, a sample size of 196 patients (per arm) and a percentage bleeding events of 1% in the control group and an expected percentage bleeding events of 1% in the experimental group will result in a power of 80% to exclude that there is a significant bleeding rate in the experimental arm (> 3.5% bleedings, absolute risk increase 2.5%, two group *t* test with a 0.05 two-sided significance level). As we do not anticipate any loss to follow-up – considering the short time-span of the study – we therefore intend to enrol 392 patients in total.

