### Statistical analysis

Statistical analysis will be based both on an intention-to-treat principle and a per-protocol approach. Baseline assessments and outcome parameters will be summarised using simple descriptive statistics. The main analysis focusses on a comparison between the trial treatment groups of the primary outcome, the occurrence of relevant bleedings, expressed in a relative risk estimate and absolute risk increase, with the associated 95% upper confidence limit. Non-inferiority is demonstrated if this interval does not exceed the non-inferiority limit of 2.5% absolute difference in favour of transfusion.

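### The 80% power comes from a t-test formula with about 2 expected events per arm; at 196 per arm, score limits that hold about 5% one-sided error have about 63% power

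*Protocol article*

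**What the plan says.** In the protocol article, *Statistical considerations* bases the trial size on "a sample size of 196 patients (per arm) and a percentage bleeding events of 1% in the control group". The experimental arm is given "an expected percentage bleeding events of 1% in the experimental group". It then states that this "will result in a power of 80% to exclude that there is a significant bleeding rate in the experimental arm", and specifies the calculation as "> 3.5% bleedings, absolute risk increase 2.5%, two group *t* test with a 0.05 two-sided significance level".

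*Statistical analysis* sets the decision rule. The primary outcome is summarised as a relative risk and an absolute risk increase "with the associated 95% upper confidence limit", and non-inferiority is declared if that limit stays within 2.5 percentage points. No method is named for the limit. The t test appears only in the sample-size sentence.

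**The concern.** The outcome is binary and rare. With 196 patients at 1%, each arm is expected to have 196 × 0.01 = 1.96 events. At such counts the t test and the simple normal (Wald) interval estimate the variance poorly, and the upper limit tends to sit too low. The power given by the formula may then be available only at an error rate above the nominal one.

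Two things are at stake. If the limit is computed by the t/Wald route, the trial is too likely to conclude that omitting platelets is non-inferior when it is worse by exactly the margin; the Discussion says guidelines might be adjusted on that conclusion. If the limit is computed by a method that controls error, the stated chance of success is too high.

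**Working it through.** **Inputs** (*Statistical considerations* and *Statistical analysis*): n = 196 per arm; event rate 1% in both arms under the alternative; margin 2.5 points, so the design null is 3.5% versus 1%; alpha 0.05, worded as two-sided; decision by a 95% upper limit on the risk difference.

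**Step 1. Reproduce the plan's figure.** The unpooled normal formula is n = (z_α + z_β)² × 2p(1−p) / margin², with 2 × 0.01 × 0.99 = 0.0198 and margin² = 0.000625.

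- One-sided 5%: (1.645 + 0.842)² × 0.0198 / 0.000625 = 195.9, so 196 per arm.
- One-sided 2.5% (the literal two-sided 0.05): (1.960 + 0.842)² × 0.0198 / 0.000625 = 248.7, so 249 per arm.

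The standard error at 196 per arm is √(0.0198/196) = 0.01005, and 0.025/0.01005 = 2.487. Formula power is Φ(2.487 − 1.645) = 80.0% at one-sided 5% and Φ(2.487 − 1.960) = 70.1% at one-sided 2.5%. The published pair of 196 and 80% therefore belongs to one-sided 5% only.

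**Step 2. Exact operating characteristics.** Every pair of event counts is enumerated from two independent binomials with n = 196 each. A pair passes if its upper limit is below 2.5 points. Power is the probability of passing at 1% versus 1%; type I error is that probability at 3.5% versus 1%.

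| Rule at 196 per arm | Nominal one-sided level | Type I error | Power |
|---|---|---|---|
| t/Wald | 5% | 7.8% | 80.4% |
| Score (Miettinen-Nurminen, Farrington-Manning); Newcombe gives the same decisions | 5% | 4.5% | 63.5% |
| Exact unconditional test (maximum size 4.9%) | 5% | 4.4% | 63.4% |
| Agresti-Caffo | 5% | 5.1% | 71.0% |
| t/Wald | 2.5% | 5.3% | 74.7% |
| Score | 2.5% | 1.8% | 47.2% |

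**Step 3. Dependence on the control rate.** At nominal one-sided 5%, the t/Wald error is 7.8% at 3.5% versus 1%, 9.1% at 3.0% versus 0.5%, and 13.0% at 2.5% versus 0%. The score limits reach at most about 5.1%, at a control rate near 5.5%. Agresti-Caffo reaches about 5.5%, at 3.0% versus 0.5%.

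**Step 4. Where the methods disagree.** At one-sided 5% and up to 7 events per arm, Wald passes and score fails at (experimental, control) = (2,0), (2,1), (3,2), (4,4) and (6,7). Under 1% versus 1% the pair (2,1) alone has probability 7.5%. The disagreements together account for the whole gap, 80.4% − 63.5% = 16.9%. For (2,0) the Wald upper limit is 2.20% and the score upper limit is 3.04%.

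**Step 5. Sensitivity to n.** Score power moves in steps because the counts are discrete: 63.0% at 200 per arm and 69.7% at 205. At one-sided 5% it first reaches 80% at 265 per arm and stays above it from 282. At one-sided 2.5% about 357 per arm are needed.

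**The case against.** The strongest reply is that the t test is only a sample-size device. A reader might infer from the 7.8% that the planned primary analysis has an inflated error rate. The document does not support that: its analysis section prescribes a confidence limit without naming a method, and a statistical analysis plan that is not shown may name a sound one. This stands. The 7.8% is conditional on a Wald or t interval being used, and the missing method name is not itself a finding.

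It can also be said that 80% is not an arithmetical slip, since the exact power of the named rule is 80.4%. That is true, but the same rule carries 7.8% error. A different analysis method would control the error and lower the power, so the two stated properties do not hold together.

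A reader might also take 63% as the power of any valid method. It is not that firm. It depends on the method and on n, it sits on a low step of a saw-tooth, and Agresti-Caffo gives 71% with error slightly above 5%. A fair range near this sample size is roughly 60% to 70%; none of these alternatives brings it back to 80%.

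Finally, the enrolment limit of 462 might suggest 231 per arm, where score power is 73%. The article describes 462 as the room for loss and dropout, so 231 evaluable per arm is not planned.

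**Conclusion.** The point holds in this form. The stated 80% power with 196 per arm cannot be had together with a controlled 5% one-sided error. At the design rates, the t/Wald rule gives 80% power with 7.8% error, and score-type limits give about 63% power with 4.5% error. If the two-sided 0.05 is taken literally, the score figure is 47%. The mismatch between the two-sided wording and the one-sided calculation is a separate slip in the same sentence and has to be resolved before any power can be quoted.

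The figures assume 1% in both arms, 196 evaluable patients per arm and two independent binomial samples. The article allows repeat participation and stratifies randomisation; the calculation ignores both, so the results describe the simple two-sample design that the sample-size statement itself uses.

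**What to change.** In *Statistical considerations*:

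- Remove the reference to the two-group t test.
- State alpha as one-sided 5%, to match the 95% upper confidence limit in *Statistical analysis*; or keep two-sided 0.05 and accept the lower power.
- Restate power as about 63% for 196 evaluable per arm at one-sided 5%, or about 47% at one-sided 2.5%, by exact calculation for a score limit.
- Do not present 73% at 231 per arm as planned power.

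In *Statistical analysis*, make the decision limit a Miettinen-Nurminen score upper limit for the absolute risk difference instead of a Wald or t limit. Do this before results by arm are known, because plausible event counts pass under one method and fail under the other.

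The cost is wording and a less favourable stated power. The correction itself requires no extra patients.

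### 196 per arm gives 80% power only at a one-sided 5% level; at the stated two-sided 0.05 level power is about 70%, and the non-inferiority rule does not say which level applies

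*Protocol article*

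**What the plan says.** In the protocol article, the Statistical considerations section gives every input of the sample size: 196 patients per arm (392 in total), "a percentage bleeding events of 1% in the control group", "an expected percentage bleeding events of 1% in the experimental group", an absolute margin of 2.5 percentage points, 80% power, and a two-group "test with a 0.05 two-sided significance level". It also mentions allowances of 2% for loss to follow-up and 15% for dropout, with an upper limit of 462 patients.

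The Statistical analysis section says that the primary outcome will be "expressed in a relative risk estimate and absolute risk increase, with the associated 95% upper confidence limit". The decision rule follows: "Non-inferiority is demonstrated if this interval does not exceed the non-inferiority limit of 2.5% absolute difference". It does not say whether the limit is a one-sided 95% bound or the upper end of a two-sided 95% interval.

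**The concern.** A non-inferiority conclusion uses only one end of the interval. A two-sided 0.05 level therefore means 2.5% in the relevant tail, and a one-sided 0.05 level means 5%. These are different tests: the second allows twice the risk of wrongly declaring that omitting transfusion is non-inferior, and it needs fewer patients for the same power.

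If the sample size was computed at one level and the text states the other, the claimed power is wrong for the stated test. If the decision rule can also be read either way, the pass/fail criterion of the primary analysis is not fixed. Someone who already knows the result could then choose the more favourable reading.

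**Working it through.** **Inputs**, all from Statistical considerations: event rate p = 0.01 in both arms (true difference 0), margin d = 0.025, power 80% (z = 0.8416), n = 196 per arm.

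**Formula** (unpooled normal approximation for a risk difference):

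n per arm = (z_alpha + 0.8416)² × 2p(1 − p) / d², with 2p(1 − p) = 2 × 0.01 × 0.99 = 0.0198 and d² = 0.000625.

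**The plan's own figure, at one-sided 5%** (z = 1.645):
(1.645 + 0.8416)² × 0.0198 / 0.000625 = 195.9, so 196 per arm. This matches the protocol exactly.

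**The stated level, two-sided 0.05** (z = 1.960):
(1.960 + 0.8416)² × 0.0198 / 0.000625 = 248.7, so 249 per arm (498 in total).

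**Power at 196 per arm:** the standard error is √(0.0198 / 196) = 0.01005, and 0.025 / 0.01005 = 2.487.

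| Level | Calculation | Power |
|---|---|---|
| One-sided 5% | Φ(2.487 − 1.645) | 80.0% |
| Two-sided 5% | Φ(2.487 − 1.960) | 70.1% |

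The protocol names a t test. Using the t distribution changes little: 197 per arm at one-sided 5% and 250 at two-sided 5%, with power at 196 of 79.9% and 69.9%.

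**Other methods.** Per arm, at one-sided 5% and two-sided 5% respectively:

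- continuity-corrected: 270 and 324
- restricted-variance score: 296 and 384
- equivalence (two one-sided tests): 272 and 333
- superiority of 1% versus 3.5%: 435 and 552

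None gives 196.

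**Dropout allowances.** They do not explain the gap, because 2 × 196 = 392 is the number before inflation. Even at the limit of 462 patients (231 per arm), power at two-sided 0.05 is about 77%.

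**Effect on the decision.** Upper limits for the risk difference (no transfusion minus transfusion), 196 per arm, margin 2.5%:

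| Events, no transfusion vs transfusion | Interval | One-sided 95% | Upper end of two-sided 95% | Same verdict? |
|---|---|---|---|---|
| 2 vs 2 | Score (Miettinen-Nurminen) | 2.14% | 2.74% | No |
| 2 vs 2 | Wald | 1.67% | 1.99% | Yes, non-inferior |
| 3 vs 2 | Wald | 2.37% | 2.73% | No |
| 4 vs 4 | Wald | 2.35% | 2.80% | No |

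The planning rate of 1% implies about 2 events per arm (0.01 × 196 = 1.96).

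**The case against.** The strongest reply is that only one word is wrong. Non-inferiority is a one-directional question, so a 95% upper confidence limit is naturally a one-sided bound. On that reading the decision rule agrees with 196 per arm and 80% power, and only the label two-sided is mistaken. This may well be what was intended. The text does not establish it, however: the decision sentence refers to an interval, and the only sidedness given anywhere for the primary comparison is two-sided.

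A second reply is that the example with 2 events per arm depends on the interval method, which the article does not name. That is correct. Score limits change the verdict there and Wald limits, which match the sample-size formula, do not. But Wald limits change it one event away, at 3 versus 2, so the level matters at or next to the planning result under both methods.

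A third reply is that 70% is a large-sample approximation with about two events expected per arm. This also stands as a caveat. Exact binomial power at 196 per arm is 80.4% (one-sided 5%) and 74.7% (two-sided 5%) with Wald limits, and 63.5% and 47.2% with Newcombe limits. The size of the loss depends on the method, but power is lower at the two-sided level in each case.

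Finally, the interval method may properly be left to an analysis plan that is not shown. That does not cover a significance level stated in this document that contradicts the sample size beside it.

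**Conclusion.** The concern holds. The figure of 196 per arm with 80% power is a one-sided 5% calculation, but the text calls it two-sided 0.05. At the stated level power is 70.1%, about 10 points below the claim, and 80% would need 249 per arm, or 498 patients, which exceeds both the target of 392 and the limit of 462.

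These figures rest on the protocol's own rates and margin and on the normal approximation that reproduces its sample size. With exact Wald power the shortfall between the two levels is about 6 points (80.4% versus 74.7%).

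The decision rule leaves the level of the primary test open, and the choice can reverse the conclusion at or next to the result the trial is planned around. It should be corrected before the results are known.

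**What to change.** State one level, in the same terms, in both Statistical considerations and Statistical analysis. There are two ways to do this without more patients:

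- **One-sided 0.05.** Replace two-sided by one-sided in the sample-size paragraph. Write the rule as: non-inferiority is shown if the one-sided 95% upper confidence limit for the absolute risk difference (equivalently, the upper end of the two-sided 90% interval) is below 2.5%. This keeps 196 per arm and 80% power under the normal approximation.
- **Two-sided 0.05.** Keep the label, restate the power as about 70% (normal approximation), and write the rule in terms of the upper end of the two-sided 95% interval.

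Either choice changes two sentences. The first means openly accepting a 5% one-sided error rate; the second means accepting lower stated power. Keeping both two-sided 0.05 and 80% power would instead require about 249 per arm before any dropout allowance.

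The 80% in the first option holds for the normal or Wald calculation only. With a score interval the same assumptions need 296 per arm at one-sided 5%, so the interval method should be chosen with that in mind.
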